### Outcome measurements

The primary endpoint shall be the prevalence of colorectal polyps and number of polyps after 1-year's intervention. The endoscopic examinations and polypectomies will be performed using Olympus colonoscopes (model H260AZI). The day before the endoscopy, each patient will be instructed to consume a low-residue diet and shall receive 5 mg of oral sodium picosulfate. On the day of the endoscopy, the patients shall receive 2000 ml of polyethylene glycol (PEG). If the feces are not sufficiently clear, an additional 1000 - 2000 ml of PEG may be given to ensure sufficient bowel cleaning. At the time of the polypectomies, the endoscope shall be inserted into the cecum, and the entire colorectum will be carefully observed as the endoscope is pulled back. If any polyps are detected, polypectomy will be performed. At the end of 1 year of administration of metformin/placebo, the same endoscopists will perform the repeat endoscopic examinations. If a polyp(s) is detected at the repeat colonoscopy (after treatment for one year), a biopsy will be performed. A total of 6 endoscopists from Yokohama City University Hospital and the 5 affiliate hospitals will perform the polypectomies and endoscopic examinations. All procedures will be recorded on DVD, and all the polyps will be photographed. The number of polyps in each patient will first be counted by the operators during the performance of the colonoscopy. To further ensure validity, the number of polyps will be counted again through observation of the recorded DVD by 3 blinded expert endoscopists ([name], [name], and [name]). If these expert endoscopists judge the colonoscopic examination as having been inadequate in any case, that case will be excluded. The biopsied polyps will be evaluated by expert pathologists ([name] and [name]).

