The secondary outcomes are (1) the drug safety; adverse events will be monitored by the doctor at every follow-up visit to the outpatient clinic. Adverse events will be graded according to the National Cancer Institute Common Toxicity Criteria for Adverse Events (NCI-CTCAE), version 4.0. Diarrhea, the most frequent adverse event related to use of metformin, will be watched for spontaneous resolution within a few days and/or managed by antiflatulent drugs. If Grade 3 or more severe adverse events appear, the follow-up doctor shall report it (them) to the coordinating office and the case will be withdrawn from the study at that point; (2) laboratory data (fasting blood glucose, fasting blood insulin, HbA1c, total cholesterol, LDL-cholesterol, blood urea nitrogen (BUN), creatinine); (3) the number of ACF. At the time of the 1-year colonoscopy and polypectomy, the lower rectal region from the middle Houston valve to the dentate line will be washed thoroughly with water, sprayed with 0.25% methylene blue, which would be left to stand for 2 min, then again washed thoroughly with water. The number of rectal ACF will be counted with a magnifying endoscope [21]; (4) physical examination findings (body weight, body mass index (BMI)). Metformin is widely used as an antidiabetic drug that improves insulin resistance. The effect of metformin on insulin resistance and the plasma lipid profile will be evaluated by comparing these parameters measured at the baseline and at 1 year in the metformin group and placebo group. All participants will receive physical examination and laboratory tests at the time of the 1-year endoscopic examination and polypectomy; (5) effects of metformin on the cell-proliferative and apoptotic activities in the rectal epithelium and polyps (if any). Colonic epithelial samples will be obtained from the same trial patients by biopsy at the time of the 1-year colonoscopy and polypectomy. The cell-proliferative activity will be evaluated by staining for the proliferative cell nuclear antigen (PCNA), and the cell-apoptotic activity by the terminal deoxynucleotidyl transferase-mediated dUTP-biotin nick end labeling (TUNEL) method; (6) expression levels of protein (AMPK, mTOR/S6K) in the rectal epithelium and polyps (if any) that are thought to be pharmacological targets of metformin. The expression levels of these proteins shall be determined by western blot analysis.

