### Sample size estimation

We previously showed that metformin administered at 250 mg/d for 1 month directly suppressed the formation of ACF. In that study, mean number of ACF per patient decreased significantly from 8.78 ± 6.45 (baseline) to 5.11 ± 4.99 (at 1 month, *p = 0.007*) [20]. Based on a similar study, Takayama et al. reported that sulindac administration at 300 mg/d for 2 months to post-polypectomy patients suppressed ACF formation, decreasing the number of ACF from 7.70 ± 4.04 (baseline) to 4.00 ± 2.95 (at 2 months, *p < 0.001*) [26]. From these reports, we estimated that metformin and sulindac may have equivalent effect on suppression of ACF formation. Moreover, from the same study, Takayama et al. reported that in the post-polypectmoy patients who received 2-months' intervention, the number of polyps (hyperplastic polyp and adenoma) at 1 year after the treatment was significantly lower in the sulindac group in comparison with that in the placebo group (26/48 (54.2%) vs. 15/48 (31.3%), *p = 0.025*) [26]. Therefore, we speculated that 1-year's treatment with metformin might yield equivalent suppression of metachronous polyp formation to that with sulindac. To detect the reduction in the number of metachronous polyps in the metformin group using the chi-square test with a two-sided significance level of 5% and a power of 80%, it was found that a sample size of 68 patients per group would be necessary. Assuming a 10% dropout rate, we propose to recruit 75 patients per group, that is, a total of 150 patients.

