### Statistical analysis

The prevalence of polyps in each group, the primary endpoint, will be compared between the metformin group and placebo group by the chi-square test. The safety, one of the secondary endpoints, will be similarly compared by the chi-square test. The remaining results in the two groups will be compared by the Mann-Whitney *U *test or Student's *t *test. A P value of < 0.05 shall be regarded as indicative of significance. The analysis will be performed using SPSS, version 17.0 (SPSS Inc., Chicago, Il.).

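### Marker comparisons in polyp tissue (secondary outcomes 5 and 6) include only patients who formed a polyp, so randomisation does not protect them if metformin changes polyp formation

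*Protocol article*

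**What the plan says.** All references are to the protocol article.

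- **Outcome measurements, secondary outcome 5** covers PCNA and TUNEL, described as "effects of metformin on the cell-proliferative and apoptotic activities in the rectal epithelium and polyps (if any". Secondary outcome 6 covers AMPK and mTOR/S6K protein levels "in the rectal epithelium and polyps (if any) that are thought to be pharmacological targets of metformin".
- **Where the tissue comes from.** For epithelium: "Colonic epithelial samples will be obtained from the same trial patients by biopsy at the time of the 1-year colonoscopy and polypectomy". For polyps: "If a polyp(s) is detected at the repeat colonoscopy (after treatment for one year), a biopsy will be performed". Epithelium is thus sampled whether or not a polyp is found; polyp tissue is not.
- **Primary endpoint, same section:** "The primary endpoint shall be the prevalence of colorectal polyps and number of polyps after 1-year's intervention". The event that supplies polyp tissue is the event the trial is designed to reduce.
- **Statistical analysis** assigns the chi-square test to polyp prevalence and safety. For everything else, "The remaining results in the two groups will be compared by the Mann-Whitney" U test or Student's t test, with P < 0.05 as the criterion. Polyp-tissue markers are not set apart.

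**The concern.** Minimisation makes the arms comparable over everyone allocated. It does not make polyp formers in one arm comparable with polyp formers in the other once the drug influences who becomes one. If metformin works, its polyp sample holds only lesions that formed despite treatment, while the placebo sample holds all that would have formed.

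A marker related to susceptibility can then differ between the two samples although the drug never acted on it. A real action on the marker can also be hidden. A link between marker and susceptibility is plausible on the article's own account: its Discussion presents AMPK activation, mTOR inhibition and reduced proliferation as the route to fewer polyps. At stake is whether a difference seen in polyps can be read as a drug effect.

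**Working it through.** **Inputs from the article**
- Polyp rates (Sample size estimation): 26/48 = 54.2% and 15/48 = 31.25%, printed as 31.3%. By the sense of the sentence the first is placebo and the second active. Both reproduce.
- 68 evaluable patients per group (75 recruited, 10% dropout). This is used here only as a head count and is not in dispute on this point. The same rates at two-sided 5% and 80% power give 70 with unpooled variance and 72 with pooled variance, which would move the counts below by only one or two patients.

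**Step 1: who contributes polyp tissue**
- Placebo: 68 × 26/48 = 36.8, about 37 patients.
- Metformin: 68 × 15/48 = 21.25, about 21 patients.
- Share of would-be contributors removed by the drug: 1 − 15/26 = 42%.

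**Step 2: shift in the marker with no drug effect on it**

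This needs an assumption that the documents do not supply: a correlation ρ between the marker and a latent susceptibility. Two selection models were used.

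*Threshold model.* A polyp forms when a standard-normal susceptibility exceeds a cut-off, and metformin only raises the cut-off. Mean susceptibility among formers is φ(t)/p.
- Placebo: p = 0.5417, mean 0.73.
- Metformin: p = 0.3125, mean 1.13.
- Difference 0.40 SD; the marker shift is 0.40ρ.

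*Prevention model.* Among patients who would form a polyp on placebo, metformin keeps the least preventable 15/26 = 57.7%. The marker correlates at ρ with preventability within that group. The mean of the upper 57.7% of a standard normal is 0.3915/0.577 = 0.68; the marker shift is 0.68ρ.

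**Step 3: how often the planned test is falsely significant**

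The t-test results below are from simulations, mostly 6,000 to 8,000 runs per scenario. Ranges show the spread over repeat simulations.

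| Assumed ρ | Threshold: shift (SD) | Threshold: P < 0.05 | Prevention: shift (SD) | Prevention: P < 0.05 |
|---|---|---|---|---|
| 0 | 0 | about 5% | 0 | about 5% |
| 0.3 | 0.12 | 7% | 0.20 to 0.21 | 11% to 12% |
| 0.5 | 0.20 | 12% to 13% | 0.34 | 23% to 24% |
| 0.7 | 0.28 | 22% to 23% | 0.47 to 0.48 | 43% to 44% |

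Mann-Whitney in the threshold model gave almost the same rates (5.1%, 7.3%, 11.4%, 22.7%).

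**Step 4: the contrast without selection**

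Comparing the same simulated marker in all patients of both arms kept the rate at 4.7% to 5.2% for every ρ. The inflation therefore comes from restricting to polyp formers, not from the test.

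**Direction.** The sign of the shift follows the sign of ρ. If a proliferation marker is higher in more susceptible patients, polyps in the metformin arm would look more proliferative, which would mask or reverse a true reduction.

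**The case against.** The strongest reply is about weight. Only the polyp half of the last two of six secondary outcomes is touched. The same markers are already measured in rectal epithelium without regard to polyp formation, and the qualifier on polyps suggests that the authors see that tissue as opportunistic. Nothing in the article powers it or calls it confirmatory. All of this stands, and it makes this a point about secondary mechanistic evidence.

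The second reply is about size. Bias requires both that metformin changes polyp formation and that the marker tracks susceptibility; if either fails there is none. No document gives a correlation, and the two models differ by a factor of about 1.7 in the shift (0.68/0.40). This also stands, so the result is given as a range that includes zero.

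The third reply is that labels and caveats belong in the full protocol or analysis plan. That does not remove the point. The article does more than stay silent: it names polyp-tissue results as effects of the drug and assigns all remaining results to a significance test.

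The sampling sentence could also mean that tissue is taken at the baseline polypectomy. The 1-year polyp comparison would still be confined to polyp formers.

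**Conclusion.** The point holds. As written, the plan tests the arms against each other in a subgroup defined by the primary outcome, and that comparison is not randomised if metformin affects polyp formation. The inflation runs from none at zero correlation, through about 7% to 12% at 0.3 and 12% to 24% at 0.5, to about 22% to 44% at 0.7. The contributor counts follow from the planning rates; the correlations and both selection models are assumptions.

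A reader might infer more than the documents support:

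- *That the polyp-tissue result will be spurious.* It can be; whether it is depends on an unknown correlation and on the drug working.
- *That several polyps per patient will be analysed as independent values.* The article states no unit of analysis, and one value per patient fits its wording equally well.
- *That rectal epithelium is an unbiased test of the same mechanism.* It is a different tissue, and an effect there need not equal the effect in polyps. It also loses patients withdrawn for Grade 3 or worse events and may lose those excluded for inadequate colonoscopy. What it avoids is selection by polyp formation.
- *That any P value in polyp tissue must be forbidden.* Labelling it exploratory and conditional is enough.

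**What to change.** In Outcome measurements, items 5 and 6, name the rectal epithelium as the main between-arm mechanistic comparison. State that polyp-tissue markers are exploratory and conditional on having formed a polyp. In Statistical analysis, take polyp-tissue markers out of the general two-group testing sentence. Report them by arm with the number of contributing patients, without wording that attributes a difference to metformin.

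The cost is a sentence or two in each section, with no further samples, staff or patients. The downside is that polyp tissue would no longer support a formal treatment-effect claim, although the protocol lists it as a target tissue.

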### Randomization

The investigator shall convey the patient's details to the central registration centre via fax. After an eligibility check, the patients will be randomly assigned to receive metformin or placebo at the central registration centre by a computer program, using a minimization method, with stratification by institute, age, gender and BMI. In this way, the patient assignment will be concealed from the investigator. The randomization center will allocate a numbered treatment pack to each patient, which will contain all the drugs or placebos needed to complete a course of the trial treatment for one patient.

### Drug supply

Metformin will be purchased from Dainippon Sumitomo Parma Co., Ltd. The placebo (250 mg lactose) will be purchased from Kokando Co., Ltd, Toyama, Japan. All trial drugs will be packaged identically and identified only by number. Subjects will be instructed to take one tablet of the trial drug after breakfast every day, and to visit the hospital every 4 weeks for evaluation of the subjective symptoms and for receiving a new supply of medication. Compliance will be monitored by counting the empty drug packages returned by the patients at every visit to the outpatient clinic.

### Sample size estimation

We previously showed that metformin administered at 250 mg/d for 1 month directly suppressed the formation of ACF. In that study, mean number of ACF per patient decreased significantly from 8.78 ± 6.45 (baseline) to 5.11 ± 4.99 (at 1 month, *p = 0.007*) [20]. Based on a similar study, Takayama et al. reported that sulindac administration at 300 mg/d for 2 months to post-polypectomy patients suppressed ACF formation, decreasing the number of ACF from 7.70 ± 4.04 (baseline) to 4.00 ± 2.95 (at 2 months, *p < 0.001*) [26]. From these reports, we estimated that metformin and sulindac may have equivalent effect on suppression of ACF formation. Moreover, from the same study, Takayama et al. reported that in the post-polypectmoy patients who received 2-months' intervention, the number of polyps (hyperplastic polyp and adenoma) at 1 year after the treatment was significantly lower in the sulindac group in comparison with that in the placebo group (26/48 (54.2%) vs. 15/48 (31.3%), *p = 0.025*) [26]. Therefore, we speculated that 1-year's treatment with metformin might yield equivalent suppression of metachronous polyp formation to that with sulindac. To detect the reduction in the number of metachronous polyps in the metformin group using the chi-square test with a two-sided significance level of 5% and a power of 80%, it was found that a sample size of 68 patients per group would be necessary. Assuming a 10% dropout rate, we propose to recruit 75 patients per group, that is, a total of 150 patients.

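### For the named chi-square test at the cited rates, 80% power needs 72–73 evaluable patients per group; the stated 68 gives about 77–78% (minor; correct the text, not the enrolment)

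*Protocol article*

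**What the plan says.** All the inputs stand in the protocol article, mainly under Sample size estimation.

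- **Test, level and power:** the size was found "using the chi-square test with a two-sided significance level of 5% and a power of 80" per cent. The Statistical analysis section names the same test for the primary endpoint: polyp prevalence "will be compared between the metformin group and placebo group by the chi-square test". Neither section mentions a continuity correction.
- **Rates:** the sulindac study is reported as "26/48 (54.2%) vs. 15/48 (31.3" per cent). The sentence says that the sulindac group was the lower one, so 54.2% belongs to placebo and 31.3% to sulindac.
- **Link to this trial:** one year of metformin "might yield equivalent suppression of metachronous polyp formation to that with sulindac". No other rates are offered, so these are the planning rates by implication.
- **Result:** for "a power of 80%, it was found that a sample size of 68 patients per group would be necessary", followed by "Assuming a 10% dropout rate, we propose to recruit 75 patients per group, that is, a total of 150 patients".

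The section names no formula, variance form or software for the calculation.

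**The concern.** The article gives a complete set of inputs and a single result, so the result can be checked. A sample size for a chi-square comparison of two proportions should follow from the two rates, the level and the power, and 68 looked too small for these. The step from 68 to 75 also looked like multiplication by 1.1 (68 × 1.1 = 74.8) rather than division by 0.9.

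What is at stake is the accuracy of the 80% claim. Readers use stated power to judge what a null result in a small trial can mean. If it is overstated, they will credit the trial with slightly more sensitivity than it has, even when the assumed effect is exactly true. Type I error, the choice of test and the effect estimate are untouched.

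**Working it through.** **Inputs.** p1 = 26/48 = 0.5417, p2 = 15/48 = 0.3125, difference d = 0.2292, mean p̄ = 0.4271. Two-sided 5% gives z = 1.960; 80% power gives z = 0.8416. Groups are equal.

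Two quantities recur:
- A = √(2p̄(1−p̄)) = 0.6995 (pooled, under the null)
- B = √(p1(1−p1) + p2(1−p2)) = √0.4631 = 0.6805 (unpooled, under the alternative)

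**Step 1: try to reproduce 68.** The simplest approximation uses the unpooled variance throughout:

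n = (1.960 + 0.8416)² × B² / d² = 7.849 × 0.4631 / 0.05252 = 69.2, so 70 per group.

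The printed percentages give 69.3, again 70. Power at 68 by this route is Φ(d√68/B − 1.960) = Φ(0.817) = 79.3%. This lies within two patients of 68. Rounding both rates to 54% and 31% gives 68.6 (69). Using 54.2% with 31% gives 67.4, so exactly 68, but the article prints 31.3%.

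**Step 2: the formula that matches the named test.** The uncorrected chi-square statistic uses the pooled variance under the null, so:

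n = [1.960·A + 0.8416·B]² / d² = (1.3711 + 0.5727)² / 0.05252 = 71.95, so **72 per group**.

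With 0.542 and 0.313 it is 72.07, so **73 per group**. An arcsine calculation also gives 72.

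**Step 3: power of the uncorrected chi-square test at the planned sizes.** Power = Φ[(d√n − 1.960·A)/B]. At n = 68 this is Φ[(1.8898 − 1.3711)/0.6805] = Φ(0.762) = 77.7%. The exact column sums the binomial probabilities of all tables that the test would reject.

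| Evaluable per group | Pooled formula | Exact |
|---|---|---|
| 67 | 77.1% | 76.2% |
| 67.5 (= 75 × 0.9) | 77.4% | – |
| 68 | 77.7% | 77.2% |
| 71 | – | 79.9% |
| 72 | 80.0% | 80.7% |
| 75 (no dropout) | 81.6% | 83.1% |

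By exact enumeration, 72 is the smallest size that reaches 80%, in agreement with step 2.

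**Step 4: dropout.** To retain 68 after 10% loss, 68/0.9 = 75.6, so 76 per group. The planned 75 leaves 75 × 0.9 = 67.5. To retain 72 or 73 would take 72/0.9 = 80 or 73/0.9 = 81.1 (82) per group.

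**The case against.** **The 68 is close to a standard approximation.** The unpooled formula comes within two patients of it and gives 79.3% power there. An article need not name its formula, and most of the gap (69.2 against 71.95) comes from the choice of variance. This stands, and it rules out calling 68 a gross miscalculation. It does not make the statement right: even the unpooled formula rounds up to 70 at the printed rates, and it is not the formula for the chi-square test that the article names twice.

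**The planning rates are inferred and imprecise.** They come from 48 patients per arm in another study. Small changes move the answer: at 54% versus 30% the pooled formula gives 66 per group, and 68 then has 81.7% power. This limits how much weight a gap of 4 to 5 patients can bear. Still, the article offers no other rates, and its power statement has to hold at the rates it gives.

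**Stronger readings that the document does not support:**
- A reader might infer that 150 randomised patients simply deliver 77% power. That holds only if the full 10% is lost; with no loss the figure is about 82%.
- A reader might quote a power near 71%, which is what a continuity-corrected chi-square or Fisher's test would give. The article names neither.
- A reader might take the printed order of the two rates, or the description of patient proportions as a number of polyps, as signs of a wrong calculation. The sentence itself says which arm was lower, and the Statistical analysis section compares prevalence. Both are clerical.

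**Conclusion.** The concern holds as a minor error. For the uncorrected chi-square test of 54.2% against 31.3% at two-sided 5%, 80% power needs 72–73 evaluable patients per group, not 68: a shortfall of 4 to 5 per group. Power at 68 is 77–78%, and after the planned 10% loss about 76–77%, which is 2 to 4 points below the stated value. The dropout step adds about one patient per group and roughly 0.3 points by the pooled formula (77.7% at 68, 77.4% at 67.5).

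This rests on three assumptions: that the sulindac study's rates are the design rates, that the chi-square test is applied without correction, and that dropout reaches the full 10%. A reader might infer that the trial is seriously underpowered or must enrol more patients. A gap of this size does not support that.

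**What to change.** Keep enrolment at 150 and correct the text under Sample size estimation. Suggested wording:

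> *75 patients per group, about 67 evaluable after 10% dropout, give about 77% power (about 82% with no dropout) for the uncorrected chi-square test, two-sided 5%, of 54.2% (placebo) versus 31.3% (metformin) of patients with at least one polyp.*

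This removes the unsupported 68, deals with the dropout arithmetic, assigns each rate to its arm and describes the rates as proportions of patients. The cost is one sentence and a stated power about three points lower. Should the sponsor prefer to keep the 80% claim after 10% loss, the consistent figure is 80 to 82 randomised per group (160 to 164 in total); the size of the gap does not require this.
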